## Abstract

**Introduction:**

Provision of palliative care is inequitable with wide variations across conditions
and settings in the UK. Lack of a standard way to classify by case complexity is
one of the principle obstacles to addressing this. We aim to develop and validate
a casemix classification to support the prediction of costs of specialist
palliative care provision.

**Methods and analysis:**

Phase I: A cohort study to determine the variables and potential classes to be
included in a casemix classification. Data are collected from clinicians in
palliative care services across inpatient hospice, hospital and community settings
on: patient demographics, potential complexity/casemix criteria and patient-level
resource use. Cost predictors are derived using multivariate regression and then
incorporated into a classification using classification and regression trees.
Internal validation will be conducted by bootstrapping to quantify any optimism in
the predictive performance (calibration and discrimination) of the developed
classification. Phase II: A mixed-methods cohort study across settings for
external validation of the classification developed in phase I. Patient and family
caregiver data will be collected longitudinally on demographics, potential
complexity/casemix criteria and patient-level resource use. This will be
triangulated with data collected from clinicians on potential complexity/casemix
criteria and patient-level resource use, and with qualitative interviews with
patients and caregivers about care provision across difference settings. The
classification will be refined on the basis of its performance in the validation
data set.

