**Trial registration number:**

ISRCTN90752212.

Strengths and limitations of this studyThis is the first study in the UK to determine the variables and potential classes
to be included in a casemix classification, which predicts costs of specialist
palliative care provision across inpatient hospice, hospital and community
settings.Transparent Reporting of a multivariable prediction model for Individual Prognosis
Or Diagnosis is used to guide the reporting of this study.The newly developed casemix classification in phase I will be externally validated
by using a different data set in phase II.This study also promotes the implementation of outcome measures in palliative care
into routine clinical practice across different settings of care.This is a UK-focused study so the casemix classification may not be directly
applied to palliative care in other countries without further investigation and
refinement.

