### Participants

#### Phase I: development phase

All adults (≥18 years) receiving specialist palliative care newly admitted
in 10 participating sites during the study period (two sites providing hospital
advisory services, one providing community-based service only, six providing
hospice inpatient and community-based services, one providing hospital advisory
and community-based services) were included, regardless of primary diagnosis. We
selected these sites with the aim of ensuring a representative sample in terms of
population demographics (age distribution, ethnicity, socioeconomic status and
rural/urban composition). Written informed consent was taken by a qualified member
of the research or clinical team. This phase included individuals with limited,
fluctuating, diminishing or lack of capacity, vital to ensure that any casemix
classification is applicable to all palliative patients, not just those able to
consent. It is recognised that a high proportion of those have impaired capacity,
and these patients may need palliative care and resources most.^20–23^ Therefore, if the
clinician assessed that the patient did not currently have the capacity to give
consent, assent was sought from an accompanying family member, or failing that, a
staff member to whom the patient was known. Where a formally appointed power of
attorney existed, this took precedence.

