#### Phase II: validation phase

All adults (≥18 years) receiving specialist palliative care newly admitted
from 14 sites during the study period (participating sites in phase I, but
extending to four additional sites to increase recruitment) will be eligible,
regardless of primary diagnosis. Additional sites were accepted if they could
contribute to maintaining or extending representativeness in terms of population
demographics (age distribution, ethnicity, socioeconomic status and rural/urban
composition). Written informed consent will be sought from eligible patients (and
their family caregivers) at the outset, including advance consent for study
follow-up if capacity is lost. This study is of minimal risk with participants not
exposed to undue harm.^24^

For both phase I and II, a list of study sites can be obtained via https://www.kcl.ac.uk/nursing/departments/cicelysaunders/research/studies/c-change/c-change.aspx.

Since transition of care is important for casemix, patient participants who
transfer between settings (and caregiver participants) will be followed up. We
will verbally confirm continuing consent with each participant when making such
contact. If capacity of patient participants is lost, we will seek advice from a
personal consultee on whether the patient should remain in the study to verify no
change of decisions has been expressed by the patient prior to loss of capacity.
On recruitment, participants will be asked if they are willing to be interviewed
at a later stage. To capture variation in age, gender, diagnosis and geographical
location, we will purposively select 20–25 patients and family caregivers
with at least two transitions of care for face-to-face interviews. Each
semistructured interview will last 40 min, but will be guided by each
participant. In order to provide information on how care transitions might be
better negotiated to improve outcomes and experiences, the interviews will cover
communication, coordination of care, information/support needs, discharge planning
and experience of transitions.

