#### Predictors collected from patients and family caregivers

Variables (table 3) will be collected in
the validation phase from patients/caregivers using face-to-face/telephone
contacts and postal questionnaires according to their preferences.
IPOS patient version and Distress Thermometer will be collected from
patients at the start of episode, at change of phase of illness and at the end of
episode. Views on Care and Short-Form Health Survey V.2.0 (SF-12v2) will be
collected at the start and end of each episode of care. Selected questions
capturing experiences of integrated care^42^
will be collected at the end of episode only.

**Table 3 T3:** Predictors collected from patients and family caregivers in validation phase
only

Data collection from patients	Data collection from family caregivers
IPOS patient version	Basic demographic information
Distress Thermometer	Distress Thermometer
Views on Care	Two caregiver questions
SF-12v2*	Zarit six items
Patient experiences of integrated care	

*The measure could be completed by a family caregiver if the patient is
too unwell to complete.

SF -12v2, Short-Form Health Survey V.2.0.

All caregiver- reported measures will be collected at the start of episode, at
change of phase of illness and at the end of episode. Where phase length exceeds 4
weeks, data collected from patients (and caregivers) will be captured as a change
of phase. If the patient is transferred to an out-of-scope inpatient setting, we
will follow up with the patient when he or she gets home and
retrospectively collect minimum information about this episode of care.

If the patient is deceased, data such as SF-12v2 and Pall-CSRI will be collected
from the participating caregiver three months after death by postal
questionnaire, along with the bereavement support information and contacts. The
time between death and the postal questionnaire may influence caregivers’
willingness to share their views; shorter periods possibly being too upsetting to
contemplate involvement.^43^ There is mixed
evidence of the best time to make contact with potential participants for
follow-back surveys^44 45^ and 3–4
months post bereavement is considered acceptable by bereaved families.^30^

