### Model development

The distribution of casemix criteria (cost predictors) in the participant population
will be described based on phase of illness, functional status and problem severity,
using parametric or non-parametric statistics, as appropriate. In order to reduce the
number of cost predictors, we will initially use univariate analysis to explore the
association and strength of association between casemix criteria and cost of the
episode of care (quantifying cost by per diem cost, per phase cost and total cost of
episode). We will use generalised linear model (multivariate regression model) to
select variables that will then be applied in a hierarchical manner to form a
branching classification in which each cost driver is incorporated only once.

We will select variables according to how much of the predictive error
(R^2^) each variable predicts and the related P value. After each
bootstrap iteration, we will rank the variables according to these two criteria and
remove the weakest (non-significant) predictor. Variables shown in tables 2 and 3 and the newly created
categorical variable representing ‘model of care’ will be initially
entered into the models and then non-significant predictors removed at each iteration
using a Bootstrap subsampling strategy. We will create dummy variables to enable each
level of phase of illness and model of care (categorical variables) to be assessed
individually. Internal validation will be conducted by using such methods as
bootstrapping or cross-validation to quantify any optimism in the predictive
performance (calibration and discrimination) of the developed classification.

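### Phase II can externally validate the phase I classification, but not a version refined on phase II data or one that includes Table 3 predictors

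*Protocol article*

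**What the plan says.** **Label.** The Abstract describes phase II as "external validation of the classification developed in phase I". The strengths list repeats this: "The newly developed casemix classification in phase I will be externally validated", using a different data set. Study design and source of data says that phase II prospectively tests the phase I classes in a new cohort.

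**Refinement.** The Abstract ends its methods paragraph by saying that the "classification will be refined on the basis of its performance in the validation" data set.

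**Predictors.** Study design and source of data limits phase I to clinician data. Table 3 is titled "Predictors collected from patients and family caregivers in validation phase" only. Yet Model development starts from "Variables shown in tables 2 and 3 and the newly created" model-of-care variable, all entered together and then reduced.

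**Sites.** Phase I used 10 sites. Phase II uses those sites, "extending to four additional sites to increase recruitment", which makes 14.

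**Capacity.** Under Participants, phase I admits people without capacity through family or staff assent. The stated reason is to ensure that any "classification is applicable to all palliative patients, not just those able to" consent. For phase II the text reads "Written informed consent will be sought from eligible patients (and" their caregivers) at entry. Advance consent and a personal consultee cover capacity that is lost later.

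**The concern.** External validation means scoring a fixed rule in data that played no part in building it. Two statements in the article give phase II a part in building the rule: the planned refinement, and the entry of Table 3 variables at model development. Once either happens, the version that results has been shaped by phase II. Its phase II performance is then apparent performance, and some optimism should be expected.

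The outputs are meant for clinicians, commissioning leads and policy makers. They would naturally take a statement that the classification was externally validated as applying to the version they are given. The article does not fix which version's phase II performance counts as the validation result, nor does it say what status a refined version would have.

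Site reuse and the consent rule bear on how far even a clean phase II test generalises: to other services, and to patients who cannot consent at entry.

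**Working it through.** **1. Can Table 3 variables enter phase I development?**

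| Section | What it fixes |
|---|---|
| Study design and source of data | Phase I: clinician data only |
| Table 3 | Nine items (five patient, four caregiver), validation phase only |
| Model development | Tables 2 and 3 plus model of care entered initially |

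The three statements cannot all hold for phase I. A model with any Table 3 item can be selected and fitted only in phase II. Table 2 items do not have this problem, because phase II clinicians record the same variables as in phase I.

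**2. Is there a data set left to test a refined version?** The article describes two cohorts, no third cohort and no split of phase II. Bootstrapping and cross-validation are named only as internal validation. None of the described data would therefore be independent of a refined version.

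**3. Site overlap.** 10 + 4 = 14. Reused: 10/14 = 71%. New: 4/14 = 29%. Performance in the 10 is temporal validation in the same services. The Model of care section says that model of care may drive cost more than patient-level variables do, so this distinction matters.

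**4. The plan's phase II size.**
- Per setting: 50 + 8 × 8 = 114 episodes; 114/3 = 38 participants.
- Three settings: 3 × 38 = 114 participants; 114/(1 − 0.5) = 228; 228 × 3 = 684 episodes.
- Inflation: 228/(1 − 0.25) = 304, in line with the stated 300.

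The chain reproduces. The 684 is counted before the 50% attrition; after it, 114 × 3 = 342 episodes remain across settings.

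**5. How much optimism could refitting bring?** This is an illustration, not a figure from the plan. It assumes a normal linear model, true R² = 0.13 (the plan's effect size) carried by 8 predictors, independent episodes, and all p predictors refitted on phase II data without selection. Results are means over 1,500 simulated data sets, shown as apparent R² / R² in new data.

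| Episodes | p = 8 | p = 20 |
|---|---|---|
| 114 (one setting) | 0.19 / 0.05 | 0.28 / −0.07 |
| 342 (three settings, after attrition) | 0.15 / 0.11 | 0.18 / 0.07 |
| 684 (three settings, before attrition) | 0.14 / 0.12 | 0.16 / 0.10 |

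Closed-form check at n = 342, p = 8:
- Apparent: 1 − 0.87 × (n − p − 1)/(n − 1) = 1 − 0.87 × 333/341 = 0.15.
- New data: 1 − 0.87 × [1 + 1/n + p/(n − p − 2)] = 1 − 0.87 × (1 + 1/342 + 8/332) = 0.11.

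Both agree with the simulation.

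**The case against.** The strongest reply is that the article's label is narrow. The Abstract, the strengths list and the design section each claim external validation for the classification developed in phase I. Refining on its performance presupposes that this version is scored in phase II first, and Model performance says that performance is assessed in both data sets. This stands. A reader might infer that the final classification can never be externally validated, or that its published performance will be overstated. The text supports neither. If phase II leads to no change, the validated version is the final one, and nothing says that a refined version's phase II figures will be presented as external validation.

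A reader might also treat site reuse as enough to defeat the label. It is not. The overlap is openly stated, phase II recruits newly admitted patients after phase I recruitment closed, and four sites are new. The overlap limits geographical independence and no more.

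Nor is it right that people with impaired capacity are absent from phase II. Those who lose capacity after consenting can remain. Only those lacking capacity at entry have no described route.

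Finally, the size of the optimism is open, because the article does not say what refinement involves. Treating it as fresh selection from some 30 candidates at 304 episodes would be tempting, but 304 is phase I's net size per setting (450 × 0.75 × 0.9), and the plan expects only 5–8 variables in the final classification. Minor adjustments to classes would bring less optimism than the full refit shown; data-driven selection or correlated episodes could bring more.

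The reply does not remove the conflict between Table 3 and Model development, or the lack of independent data for whatever refinement produces. The unseen full protocol or Figure 1 may set out the sequence, but the conflicting statements are in the article itself.

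**Conclusion.** The point holds in a limited form and should be fixed. Phase II, as described, can externally validate the version built in phase I from Table 2 variables and model of care. It cannot do so for a version refined on phase II data or for one containing any of the nine Table 3 items. That conclusion rests on the text and on no simulation.

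Under the stated assumptions at 342 episodes, the gap between apparent and new-data R² is about 0.04 with 8 predictors (0.149 − 0.107) and 0.11 with 20 (0.181 − 0.073). It is larger at 114 episodes in one setting and smaller at 684.

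Two scope limits go with it: in 71% of phase II sites the test is temporal, and the validation covers patients able to consent at entry, although the article calls including people without capacity vital.

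**What to change.** - Reconcile Study design, Table 3 and Model development so that phase I development uses Table 2 variables plus model of care.
- Lock that classification, with a date, before phase II data are analysed.
- Report the locked version's phase II performance as the validation result, with the four new sites and the 10 phase I sites shown separately.
- Analyse Table 3 variables as incremental value over the locked classes.
- Label any refined version as updated and internally validated only, with optimism correction, and say that it still needs external validation.
- State that the phase II validation covers patients able to consent at entry, including those who later lose capacity.

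**Cost.** Changes of wording, a dated lock, a little more analysis, and a more modest claim for a refined version. No new data are needed and the sample size does not change. Results for the four new sites alone will be less precise than the overall result.

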**Ethics and dissemination:**

The study has been approved by the National Health Service Health Research
Authority Research Ethics Committee. The results are expected to be disseminated
in 2018 through papers for publication in major palliative care journals; policy
briefs for clinicians, commissioning leads and policy makers; and lay summaries
for patients and public.

**Trial registration number:**

ISRCTN90752212.

Strengths and limitations of this studyThis is the first study in the UK to determine the variables and potential classes
to be included in a casemix classification, which predicts costs of specialist
palliative care provision across inpatient hospice, hospital and community
settings.Transparent Reporting of a multivariable prediction model for Individual Prognosis
Or Diagnosis is used to guide the reporting of this study.The newly developed casemix classification in phase I will be externally validated
by using a different data set in phase II.This study also promotes the implementation of outcome measures in palliative care
into routine clinical practice across different settings of care.This is a UK-focused study so the casemix classification may not be directly
applied to palliative care in other countries without further investigation and
refinement.

## Introduction

People with advanced and incurable illness often suffer complex and multiple symptoms
and psychosocial concerns because of their illness or impending death.^1 2^ Their families may provide day-to-day care, as
well as be affected by their own anxieties, concerns and potential losses. These bring
increased need for health and social care, with need being defined as ‘the
ability to benefit from health or social care interventions’.^3^ Palliative care has developed to meet the needs of
these patients and families, which addresses physical/psychological symptoms and
provides social, practical and spiritual support. The UK ranks first in the 2015 Quality
of Death Index—a measure of the quality of dying in 80 countries,^4^ and the hospice movement in the UK has provided a
model of good palliative care for those in need.

However, marked inequities exist in provision of palliative care across England. Older
people and those with non-cancer diagnoses are less likely to access specialist
palliative care.^5 6^ There are also major
geographical variations, ranging from £186 to £6213 per person across
different primary care trusts in 2010,^7 8^ often
resulting in a poor match between individual needs, resources provided to meet those
needs and health outcomes achieved. With an ageing population and increasing rates of
chronic diseases, the growing healthcare burden is overwhelmingly challenging in terms
of health resource allocation around the UK.^9^ With
recognition of the constraints on resources, there is support for the systematic
approach to mapping individual needs accurately and improving the quality and efficiency
of palliative care. This has been endorsed as a high priority nationally.^7^

The Diagnosis-Related Group is a useful classification of healthcare needs driven by the
diagnosis but is inappropriate for palliative care, because palliative care needs are
not driven by the diagnosis but by factors such as functional status and symptoms.
Palliative care needs a consistent method of classifying types of patients with
complexity of needs, treatment and costs, using casemix criteria.^10–12^ It is necessary to identify those with more
complex palliative needs, requiring more resources. An Australian casemix classification
for palliative care was developed in 1997, empirically tested and progressively refined
over time.^13–15^ The Australian
casemix classification consists of classes defined by five criteria including phase of
illness, problem severity, functional status and dependency, age and model of
care, as most strongly predictive of resource use.^16^ Full class definition and categorisation are available at http://www.pcoc.org.au/. Its implementation proved the possibility of
consistently and routinely collecting data in practice in Australia.^16^ However, due to variations in outcome measures
collected and palliative care provided between countries, it is unclear whether any
existing palliative care classification can be easily applied to the UK to address unmet
needs and resolve the inequity.

This study is part of a 5-year National Institute for Health Research-funded C-CHANGE
programme (RP-PG-1210–12015). It aims to develop and validate a casemix
classification for palliative care in the UK. Specific objectives are:To determine the cost predictors of specialist palliative care, adjusting for
important confounding factors including unmet needs.To develop and validate a casemix classification for specialist palliative
care.

## Methods and analysis

The Transparent Reporting of a multivariable prediction model for Individual Prognosis
Or Diagnosis statement^17^ is used to guide
the reporting of this study protocol.

### Study design and source of data

This study consists of two phases: development phase (phase I) and validation phase
(phase II). In the analysis part of phase I, we will identify variables that predict
costs to be included in casemix classification through a cohort study with only
clinician data, and develop potential casemix classes for palliative care which will
be tested in individual episodes of care (internal validation). In phase II, we will
prospectively validate these potential classes in a new cohort study with patient,
caregiver and clinician data, and include qualitative interviews to ensure it works
during care transitions and longitudinally over the course of illness (external
validation).

